#### 2.7.1. Primary Outcomes

Blood pressure: An automatic pressure monitor will obtain the systolic and diastolic blood pressure (08A, CONTEC, Alsdorf, Germany). The participants will be evaluated based on at least 10 min of prior rest in a sitting position, with the back and arms supported and the legs without crossing, emptying the urinary bladder if necessary. In addition, women will be asked not to practice exercise, smoking, or drinking alcohol or coffee at least 30 min before the measurements. The first assessment will be taken in both arms to identify the arm with the highest blood pressure, and then two assessments will be carried out in the arm with the highest blood pressure (usually the dominant one), adding a third assessment if the difference between the measurements is greater than 5 mmHg.

Lipid profile: This will be determined in a fasting condition of at least 12 h; the extraction of 5 mL of capillary blood will be carried out by a nurse considering the necessary safeguards in the Human Performance Laboratory with the use of a meter (Cardiochek PA, USA) to determine total cholesterol, HDL cholesterol, LDL cholesterol, triglycerides, cholesterol without HDL, and total cholesterol/HDL cholesterol ratio.

Frequency of food consumption: The nutritional assessment will be carried out using the survey on eating habits, modified for use in older people, and validated by the Delphi method based on the judgment of 25 experts in nutrition [27]. The survey aims to measure the eating habits of older people and is made up of two areas of self-application. The first is composed of 12 items with a minimum score of 1 and a maximum score of 5 per question (Likert scale), which indicates the frequency of healthy habits, such as the frequency of consumption of recommended food groups, ranging from not consuming (1 point) up to the suggested day/week servings (5 points), with a score of the responses that varies from 12 to 60 points (higher value, better-eating habits) [27]. The second area consists of 7 items, foods or food groups identified as promoters of chronic non-communicable diseases (sugary drinks, alcohol, fried foods, fast food, sweet snacks, coffee), and a negative eating habit is added, such as adding salt to meals without tasting them; six of the questions have an identical score to the previous one (1, does not consume, to 5, more than three servings per day/week) and only one is rated from 1 to 3 (salt), reaching a value that ranges from 7 to 33 points (higher values indicate worse eating habits) [27].

Body composition: The following anthropometric measurements will be obtained: (i) body weight in kg with a digital scale (Seca 769, Germany; Accuracy of 0.1 kg); (ii) bipedal height in cm with a stadiometer (Seca 220, Germany; Accuracy of 0.1 cm); (iii) diameters (biacromial, transverse thorax, anteroposterior thorax, bi-iliocrestid, humeral, femoral) in cm with an anthropometer (Rosscraft Campbell 20; Accuracy of 0.1 mm); (iv) perimeters (head, arm relaxed, arm flexed in tension, forearm maximum, mesosternal thorax, minimum waist, maximum hip, maximum thigh, medial thigh, maximum calf) in cm using an inextensible measuring tape (Seca 201, Germany; Accuracy of 0.1 cm); and (v) skinfolds (tricipital, subscapular, supraspinal, abdominal, medial thigh, calf) in mm with a caliper (Harpenden, England; Accuracy of 0.2 mm). According to the International Society for the Advancement of Kinanthropometry (ISAK) [28], all assessments will be performed by an ISAK level II anthropometrist. Moreover, each woman’s body mass index will be calculated by dividing the body weight in kg by the bipedal height in m^2^. In addition, the percentage of fat mass and fat-free mass will be obtained using eight electrode tetrapolar bioimpedance (InBody 570^®^, Body Composition Analyzers, Seoul, Korea).

Cognitive status: This will be evaluated using the memory, phonetic fluency, and temporal-spatial orientation survey (in Spanish, MEFO) [29], which aims to determine cognitive impairment in older people. This survey classifies the participants into three levels: without cognitive impairment, with mild cognitive impairment, or with cognitive impairment. The advantage of the MEFO is that the level of schooling does not have an influence; its application is simple and brief [29]. The MEFO assesses deferred free recall, phonetic fluency with the letter P, and temporal-spatial orientation; furthermore, it has high sensitivity in the fields described and is validated for use with older people in Chile [29].

Brain activity: This will be recorded through a 64+8 channel surface electroencephalography (EEG) system (active-Two from BioSemi, Amsterdam, The Netherlands) using a mapping task and a reaction time task to measure spatial and visual-motor skills, in addition to the planning index of the participants, following previous recommendations [30].

Health-related quality of life: This will be obtained using the Health Survey Short Form (SF-36) version 2, which measures the attributes of eight health dimensions: physical function, physical role, body pain, general health, vitality, social function, emotional role, and mental health [31]. Each dimension is made up of a series of questions that together give a scale ranging from 0 (the worst health status for that dimension) to 100 (the best health status) [31].

Physical-functional fitness: This will be evaluated with the Senior Fitness Test, which allows evaluation of great reliability and easy application [32]. The order of application of the tests contemplated in the battery will be a chair stand test to assess the strength of the lower limbs, counting the number of repetitions made in 30 s. Using a 3-lb dumbbell and counting the number of repetitions made in 30 s, the arm curl test will assess upper-limb strength. A 2 min step test to assess cardiorespiratory fitness, recording the number of knee raises that reach at least an angle of 70° on the hip joint of each participant. The Chair sit-and-reach test to assess the flexibility of the lower limbs, measured in cm. The back scratch test to assess flexibility on the upper limbs, measured in cm. The timed up-and-go test to assess agility and dynamic balance, surrounding a cone at 8-ft (2.44 m) and recording time in seconds.

Following previous recommendations [33], the handgrip strength will be measured with a hydraulic dynamometer (Camry, model EH101, China). The participants will be located in a seated posture, aligned spine, shoulders adducted and without rotation, elbow flexed 90° to one side of the body, forearm, and wrist in a neutral position. The size of the hand will be considered to adjust the dynamometer, allowing a comfortable and functional grip of the instrument with an adequate closure of the metacarpal phalangeal and interphalangeal joints in the position of the fist, favoring contact between the first phalanx of the index and the thumb. Three attempts will be made for each hand, using the maximum value of the three registers. The postural balance will be obtained with a force platform (ArtOficio Ltd., Valparaíso, Chile) following previous recommendations [34]. The data will be acquired with a sampling rate of 40 Hz. The measurement of the postural balance will be carried out in a situation with open and closed eyes; each will have a duration of 30 s. Participants will be instructed to maintain the bipedal position as still as possible, with the arms relaxed at the side of the torso and the feet aligned with a separation similar to the shoulders’ width. The area and velocity variables of the center of pressure will be calculated using Matlab r2012a software (Mathworks Inc., Natick, MA, USA).

#### 2.7.2. Secondary Outcomes

Sociodemographic assessments: Age (years), academic level (primary, secondary, bachelor, master, Ph.D.), and civil status (married, separated, widowed, single, others).

### 2.8. Statistical Analysis

The Statistical Package for Social Science (SPSS) 25.0 will be used. Descriptive statistics will be performed where the summary and dispersion measures of the data will be calculated. The variables will be subjected to the Shapiro-Wilk tests for normality and Levene’s homogeneity of variance.

#### 2.8.1. Intention-to-Treat Analysis

A two-factor repeated measures ANOVA will be used to determine the effects of the intervention on the outcomes (group × time). Post-hoc tests will be performed with an alpha adjusted by Bonferroni to identify statistically significant differences. The effect sizes will be calculated utilizing Cohen’s d [35] within the group and between the groups, using the following equation: effect sizes = (post mean − pre mean)/standard deviation combined. The level of significance will be set at 5%. The intraclass correlation coefficient will be used to verify the measurement’s reliability, with a predetermined threshold of 0.80 being used to include the data in the analyses. The inter-individual variability of the intervention will be determined using previously reported criteria, and responders and non-responders will be classified using the technical error (TE) of measurement. This TE will be calculated according to the formula: TE = SD (standard deviation) dif/√2, where SD is the variance of the differences in the observed values of two repeated measurements in each test [36]. A non-responder is a person who does not show an increase or decrease (in favor of beneficial changes) in the study variable greater than twice the TE, far from zero. Thus, a shift in favor of beneficial health effects, which is <2 TE means the existence of a high probability (12 to 1 odds ratio) that the response to exercise is true [36,37]. In addition, Fisher’s exact test will compare groups of participants who were at 2 × TE calculated on each outcome as non-responders and more than twice the TE as responders [37].

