### 2.3. Sample Size Calculation

The sample size calculation indicates that the ideal number of participants per group is 16. According to previous studies [22], for this calculation, an average difference of 3.46 repetitions (chair stand test) was used as the minimum difference required for substantial clinical relevance, with a standard deviation of 3.38 repeats, considering an alpha level of 0.05 with 90% power and an expected loss of 15%. GPower software (Version 3.1.9.6, Franz Faul, Universiät Kiel, Kiel, Germany) will be used to calculate statistical power.

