#### 2.6.4. Control Group (CG)

Regarding the CG, the individuals will participate in the assessments (initial and final) and will be asked to maintain their usual activities of daily living. A research assistant will contact the participants by telephone (once a week) to inquire about their health status and monitor their activities. At the end of the intervention period, the CG will be invited to participate in a physical activity program developed at the University based on the results of this study.

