### 2.7. Outcomes and Procedures

The first meeting with the participants will be held to explain the scope and aim of the study, obtain the signature of informed consent, administer the anamnesis, and randomly assign them to the intervention groups. Next, for a week, the older women will be assessed on the variables considered for the study; later, they will participate in the designated training programs. After 16-weeks of intervention, older women will undergo the same initial assessments for one week. One of the researchers will supervise all the assessments, which will be carried out by an anthropometrist (body composition), a nurse (blood pressure, lipid profile, and frequency of food consumption), a speech-language pathologist (cognitive status and health-related quality of life), a psychologist specializing in neuroscience (brain activity), and two physical education teachers (physical-functional fitness). The evaluators will not have information about the training groups, nor will the participants know their identities (i.e., a double-blind shield). Figure 2 shows a summary of the assessments and sessions that are usually part of the intervention.

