#### 2.8.2. Analysis by Protocol

Only those volunteers who have completed more than 85% of the training sessions will be considered for this analysis. The same procedures as those indicated for intention-to-treat analysis will be conducted.

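### The two-time-point repeated-measures ANOVA leaves the measured baseline unused and, as written, counts only women with both measurements; baseline-adjusted ANCOVA is a free improvement

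*Protocol article*

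**What the plan says.** Section 2.8.1, headed Intention-to-Treat Analysis, names one method for treatment effects: "A two-factor repeated measures ANOVA will be used to determine the effects of the intervention on the outcomes". The effect is tested by the group × time term, with Bonferroni-adjusted post-hoc comparisons. No covariate is named.

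There are two measurement occasions. Section 2.7 describes a week of assessments before training and then states "After 16-weeks of intervention, older women will undergo the same initial assessments for one week". Section 2.6.4 confirms initial and final assessments for the control group.

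Section 2.3 sets 16 women per group, "considering an alpha level of 0.05 with 90% power and an expected loss of 15" per cent. The article gives no rule for a woman without a final assessment. Section 2.8.2 restricts the per-protocol set to women with more than 85% of training sessions and adds "The same procedures as those indicated for intention-to-treat analysis will be conducted", so the same model governs both analyses.

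**The concern.** Two things follow from the method that section 2.8.1 fixes.

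First, precision. With only a pre and a post value, the group × time test compares mean change between groups. Baseline enters with a fixed coefficient of 1 instead of one estimated from the data. With about 14 to 16 women per arm, chance baseline differences then add noise that a covariate would remove.

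Second, the label. The named ANOVA needs both values. A woman without a final assessment does not affect the group × time test, so the analysed set depends on retention. Loss could differ between arms: the control group gets a weekly telephone call (2.6.4), while three arms are asked to attend 48 sessions of different programmes (2.6). The Introduction cites adherence averaging 50% in government-sponsored programmes and above 90% in taekwondo studies. Adherence is not retention, but the contrast makes unequal loss a reasonable worry. If nothing is done about missing post-tests, readers would take as intention-to-treat a result that rests on women measured twice.

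**Working it through.** **Inputs.** Difference 3.46 repetitions, SD 3.38, alpha 0.05, power 90%, loss 15%, 16 per group (section 2.3); two occasions (2.6.4, 2.7); four groups (2.4). Not given, so assumed: the pre-post correlation r (range 0.3 to 0.9), two-sided testing, and whether 3.38 is the SD of a single measurement or of change (both shown).

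**The plan's own figure.** d = 3.46/3.38 = 1.024. A two-sided paired t-test at 90% power needs 13, and 13/0.85 = 15.3, so 16. The stated 16 is thus reproduced by a within-group calculation. A two-sided two-sample t-test needs 22, and 22/0.85 = 25.9, so 26. That is a separate matter, but it means the between-group comparison has no power to spare.

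**Equivalence to change scores.** In a simulated data set of 64 women, the group × time F and the one-way ANOVA F on change scores were both 0.3959 on 3 and 60 degrees of freedom.

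**Women without a post-test.** 64 × 0.85 = 54.4, so about 54 women (13.6 per group) have both values. With 10 of 64 post-tests deleted at random in the simulation, keeping the baseline-only women gave the same test as dropping them (F = 0.841, 50 residual degrees of freedom, both ways).

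**Variance ratio.** With s the SD of a single measurement, equal at both times:
- change score: 2s²(1−r)
- ANCOVA residual: s²(1−r²)
- ratio: (1−r²)/[2(1−r)] = (1+r)/2

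This is the large-sample ratio. Estimating the covariate at N = 54 multiplies it by about 1 + 1/48, so ANCOVA still gains for r below 2/(1 + 1/48) − 1 = 0.96.

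**Power for one pairwise comparison.** 14 per arm (13.6 rounded up), two-sided 0.05, no multiplicity adjustment. Noncentral t with error df 4 × 14 − 4 = 52 and noncentrality 3.46/[σ√(2/14)]. Example for change scores with σ = 3.38: 3.46/(3.38 × 0.378) = 2.71, power 76%.

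- If 3.38 is the single-measurement SD: σ = 3.38√[2(1−r)] for change and 3.38√(1−r²) for ANCOVA.
- If 3.38 is the SD of change: σ = 3.38 for change and 3.38√[(1+r)/2] for ANCOVA.

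| r (assumed) | variance ratio | 3.38 = single-measurement SD: change → ANCOVA | 3.38 = SD of change: change → ANCOVA |
|---|---|---|---|
| 0.3 | 0.65 | 61% → 80% | 76% → 91% |
| 0.5 | 0.75 | 76% → 87% | 76% → 87% |
| 0.7 | 0.85 | 93% → 96% | 76% → 82% |
| 0.8 | 0.90 | 98.8% → 99.3% | 76% → 80% |
| 0.9 | 0.95 | about 100% both | 76% → 78% |

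**Bonferroni.** The planned correction lowers these figures. The article does not say how many comparisons it covers. If all six pairs are tested at 0.05/6, the r = 0.5 row becomes about 49% → 65% under either reading of the SD.

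**Would a mixed model recover the lost women?** No. In a simulation with 10 of 64 post-tests deleted, a mixed model with a common baseline mean gave the same week-16 contrasts as ANCOVA on the completers (1.167, 1.665 and 1.385 both ways). With one baseline and one follow-up, a baseline-only woman carries no information on the week-16 group difference.

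**The case against.** The strongest reply has three parts.

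*The change-score test is valid.* With complete data, randomisation makes the comparison of mean change unbiased, and chance baseline imbalance adds variance, not systematic bias. This stands. A reader might infer that the planned test gives a wrong answer; nothing in the article supports that. The loss is one of precision.

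*The gain may be small.* The article gives no r. The ICC threshold of 0.80 in section 2.8.1 concerns measurement reliability, not a 16-week correlation, but it makes high values plausible, and at r = 0.8 to 0.9 the variance saving is only 5 to 10%. This also stands, and it is why the whole range is shown.

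*The article states no deletion rule.* A reader might infer that the plan excludes about 10 of 64 randomised women, or that it is simply a completers analysis under another name. The documents do not go that far. The 15% is a planning allowance. Handling of missing post-tests may sit in a full protocol or SAP that is not shown, and imputation before the ANOVA would be compatible with the text. Poor attenders who return for the final assessment stay in, so this set also differs from the per-protocol set. What remains is conditional: as written and without imputation, the named method uses only women with both values.

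**Conclusion.** The point holds as a recommended improvement. The analysis that section 2.8.1 fixes is a change-score comparison that leaves the measured baseline unused. Baseline adjustment cuts the variance to 65–95% of its value over r = 0.3 to 0.9. At r = 0.5 this moves power from 76% to 87% for one unadjusted comparison with 14 per arm. The gain shrinks as r rises, and the figures depend on which SD 3.38 is.

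The intention-to-treat label is justified only if missing post-tests are dealt with somewhere; as written, about 54 of 64 women would inform the result at the planned loss. It would be a mistake to conclude that switching to a mixed model cures this, because with two time points it reproduces completer ANCOVA. Baseline adjustment and missing-data handling are separate repairs. Neither gap makes the planned test invalid under randomisation with complete data, so this is not a must-fix.

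**What to change.** 1. In section 2.8.1, for each continuous outcome, replace the group × time ANOVA by ANCOVA: week-16 value on group plus the baseline value of the same outcome. Report the adjusted group differences with 95% confidence intervals and keep the planned Bonferroni adjustment. Section 2.8.2 then follows with the same model.
2. For the label, do one of two things. Either add a sensitivity analysis that includes all randomised women, such as multiple imputation with a missing-not-at-random shift, or describe the main analysis as one of women with both measurements. Section 2.7 places randomisation before the baseline week, so a woman lost in between has no outcome data, and the imputation should say how she is treated. If lost women are instead assigned zero change, this is single imputation: analysed as if observed, it understates the uncertainty.

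The cost is wording and some analysis time. No new data, visits or participants are needed, and ANCOVA is available in the SPSS version already named. The choice should be fixed before outcome data are seen.

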
On the other hand, in Chile, more than 70% of people over the age of 60 years old are classified as physically inactive [18], with women having the highest prevalence at 74.2%, and men at 54.7% [18]. Additionally, Chilean women are more sedentary (90%) and have a higher prevalence of overweight/obesity (74.8%) than men, who reach 83.3% and 73.6% for the same variables, respectively [19]. These data represent elements that would have a negative impact on the health status of Chilean older women [20]. Therefore, this study protocol aims to analyze and compare the effects of an adapted taekwondo program with respect to multi-component training and walking exercise on health status (blood pressure, lipid profile, frequency of food consumption, body composition, cognitive status, brain activity, health-related quality of life and physical-functional fitness) in independent older women. Secondarily, analyze the variability of the inter-individual response of the participants and compare according to the designated training system.

Based on previous studies [6,7,8,9,11,12,14,15,16,17] we hypothesized that: (i) adapted taekwondo produces significantly greater effects on cognitive status, brain activity, health-related quality of life, and postural balance than a multi-component training and walking exercise, and; (ii) older women who participate in the adapted taekwondo program have more favorable inter-individual responses (higher percentage of responders) in cognitive status, brain activity, health-related quality of life and postural balance compared to women who participate in a multi-component training and walking exercise.

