## 4. Conclusions

This study protocol will analyze and compare the effects of a TKD program with respect to MCT and WE on health status in independent older women. Secondly, it will analyze the variability of the inter-individual response of the participants and compare them according to the designated training system. Our hypothesis indicates that TKD produces more significant effects and greater inter-individual responses (higher percentage of responders) in cognitive status, brain activity, health-related quality of life, and postural balance than MCT and WE. If this intervention proves to be beneficial, it might be included in public and private physical activity programs for older women.

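### Hypothesis (i) sets taekwondo against two active comparators, but section 2.8.1 tests a four-arm interaction and then Bonferroni post-hoc pairs with no named contrasts or family; an all-pairs family would cost about 10 to 18 points of power

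*Protocol article*

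**What the plan says.** The Introduction states hypothesis (i) as a directional comparison with two named arms: "adapted taekwondo produces significantly greater effects on cognitive status, brain activity, health-related quality of life, and postural balance than a multi-component training and walking exercise". The control group appears in neither hypothesis, although it is one of the four randomised arms (sections 2.1 and 2.4).

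Section 2.8.1 analyses the outcomes with a two-factor repeated measures ANOVA (group by time) and then adds: "Post-hoc tests will be performed with an alpha adjusted by Bonferroni to identify statistically significant differences". It gives no list of contrasts and no number of comparisons. The overall level is given as "The level of significance will be set at 5" per cent. Hypothesis (ii), on the percentage of responders, is handled separately with Fisher's exact test.

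The Conclusions add: "If this intervention proves to be beneficial, it might be included in public and private physical activity programs for older women". The Abstract has a similar sentence about the intervention proving effective. Neither names the comparator for that judgement.

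Section 2.3 sizes the trial on the chair stand test, taking 3.46 repetitions as the smallest relevant difference and 3.38 as its SD. The error rates and attrition in that section read "considering an alpha level of 0.05 with 90% power and an expected loss of 15" per cent. It does not mention multiple comparisons.

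**The concern.** The plan has a specific question and a general search procedure, with nothing linking the two.

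- **The omnibus test does not address hypothesis (i).** With four arms, the interaction can be significant because the three exercise groups improve equally and the control group does not. Hypothesis (i) would then be false.
- **The post-hoc step gives the hypothesised contrasts no priority.** An unstated family can be settled after the data are seen. On the ordinary reading for four groups it covers six pairs. Three of them (MCT-WE, MCT-CG, WE-CG) are not part of hypothesis (i), yet they use up alpha that the two hypothesised contrasts need.

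With 16 women per arm that loss matters. A non-significant TKD-MCT or TKD-WE result would be quite likely even if the planning difference were real. A reader could easily take it as showing that the programmes do equally well, which a superiority test of this size cannot show.

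**Working it through.** **Inputs.** From section 2.3: difference 3.46, SD 3.38, 16 per group, alpha 0.05, stated power 90%, loss 15%. From sections 2.1 and 2.4: four arms with equal allocation. Assumptions: two-sided tests (sidedness is not stated), and SD 3.38 applies to the quantity compared between arms (the plan does not say whether it is the SD of raw scores or of change). With one assessment before and one after, the group by time test is equivalent to comparing mean change between arms.

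d = 3.46 / 3.38 = 1.024.

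**1. The plan's own figure.** The stated 16 is reproduced by a within-group pre-post t-test: 90% power needs n = 13, and 13 / 0.85 = 15.3, rounded up to 16. It is not reproduced by a two-sided between-arm t-test at 90% power, which needs 22 per arm before loss and 22 / 0.85 = 25.9, so 26, after it. The starting point for between-arm contrasts is therefore already below 90%.

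**2. The omnibus test when only the control group differs by d.** The effect size is f = d × √3 / 4 = 0.443. The noncentrality is f² × 64 = 12.57 at 16 per arm, with 3 and 60 degrees of freedom. The test rejects 83% of the time (77% at 14 per arm), although TKD, MCT and WE are then equal.

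**3. Power per contrast.** The noncentrality is d × √(n/2), which at n = 16 is 1.024 × √8 = 2.895. Power is the noncentral t probability beyond the two-sided critical value. It is shown with two-sample degrees of freedom (2n − 2) and, as the ANOVA would use, error pooled over four arms (4n − 4).

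| Bonferroni family | Alpha per contrast | n = 16, two-sample / pooled | n = 13.6, two-sample / pooled |
|---|---|---|---|
| Six pairs | 0.0083 | 54% / 57% | 44% / 48% |
| Three TKD contrasts | 0.0167 | 64% / 67% | 55% / 58% |
| Two hypothesised contrasts | 0.025 | 70% / 72% | 62% / 64% |
| No adjustment | 0.05 | 80% / 81% | 73% / 74% |

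The n = 13.6 columns are 16 × 0.85. Going from six comparisons to three gains about 10 to 11 points. Going from six to two gains about 16 to 18 points.

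**4. What 90% power would need** (pooled error, per arm, before / after 15% loss): six pairs 31 / 37; three contrasts 27 / 32; two contrasts 25 / 30; unadjusted 21 / 25.

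**5. Other effect sizes.** The chair stand test is not among the outcomes named in hypothesis (i), and the document gives no effect size for those outcomes. Taking d as an assumption, power at 16 per arm (pooled) for six / three / two comparisons is 33% / 43% / 49% at d = 0.8 and 10% / 16% / 20% at d = 0.5. The order is the same, but the gain in points shrinks when power is low throughout.

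**6. Precision.** The unadjusted 95% half-width for a difference between two arms of 13.6 is t(0.975; 25.2) × 3.38 × √(2/13.6) = 2.67 repetitions, against a planning difference of 3.46. An observed difference near zero would thus leave differences of more than two repetitions in either direction unexcluded.

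**The case against.** The strongest reply is that section 2.8.1 never says all pairs. The family is open, so the 0.0083 level is conditional. A condensed article may leave the list of contrasts to a statistical analysis plan. That stands as to size: the power loss is an if-then statement. It does not remove the point, because section 2.8.1 does fix a procedure (omnibus test, then post-hoc search), and that procedure is not directed at the hypothesis stated in the Introduction.

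Several stronger readings are tempting, and the document does not support them:

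- *The tests cannot answer the question.* All-pairs testing would include TKD-MCT, TKD-WE and TKD-CG with valid error control. The fault is inefficiency and lack of priority.
- *Two-sided tests of a directional hypothesis are wrong.* They are standard practice.
- *Effective or beneficial must mean better than control.* This is a reasonable inference, but neither the Abstract nor the Conclusions names a comparator, and in both the sentence directly follows the hypothesis about the other training methods.
- *Hypothesis (ii) suffers in the same way.* It is tested with Fisher's exact test, not with these post-hoc comparisons.
- *The protocol intends to claim similarity.* It states superiority hypotheses and plans no equivalence claim. The misreading is a risk, not a plan.

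It is also fair to say that the comparisons outside hypothesis (i) have some use. MCT-CG and WE-CG show whether the active comparators worked in this trial. That justifies reporting them descriptively, but not letting them dilute the alpha for the hypothesised contrasts.

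**Conclusion.** The point holds in a limited form. Hypothesis (i) concerns two contrasts. Section 2.8.1 starts from an interaction test that can be significant while that hypothesis is false, and follows it with post-hoc tests tied to no contrast and no stated family.

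If the family is six pairs, the cost is about 10 to 18 percentage points of power per hypothesised contrast compared with a family of three or two. This rests on d = 1.024 from the chair stand test, two-sided testing, and SD 3.38 applying to the between-arm comparison. For the hypothesised outcomes themselves the loss cannot be stated, because no effect size is given.

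A reader might infer that narrowing the family repairs the trial's power. It does not: even an unadjusted between-arm test has only about 80% at 16 per arm and about 73-74% after the planned loss, against the stated 90%. The sample size is a separate and larger matter.

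**What to change.** Change section 2.8.1 as follows:

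1. Prespecify TKD-MCT and TKD-WE as planned contrasts on change, estimated within the same model, as the test of hypothesis (i). They should not depend on a significant omnibus interaction.
2. Add TKD-CG if effective or beneficial is meant against no intervention, and say so. Otherwise name the comparator that those words refer to.
3. Apply Bonferroni over those two or three contrasts only, and state the number.
4. Report each contrast with its confidence interval.
5. Report MCT-WE, MCT-CG and WE-CG as descriptive.
6. State that a non-significant TKD-MCT or TKD-WE difference will not be read as similarity.

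The cost is a few sentences, with no new data and no added participants. The one downside is that MCT or WE against control could no longer carry a confirmatory claim, and the trial does not hypothesise one.

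### The between-group Cohen's d is defined by a pre-post equation with no second-group term, so as written it cannot measure a difference between groups

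*Protocol article*

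**What the plan says.** The protocol article, section 2.8.1, names the main model: "A two-factor repeated measures ANOVA will be used to determine the effects of the intervention on the outcomes (group × time"), followed by Bonferroni-adjusted post-hoc tests. It then says Cohen's d will be calculated "within the group and between the groups, using the following equation: effect sizes = (post mean − pre mean)/standard deviation combined". The one equation is assigned to both uses, and the combined standard deviation is not defined further.

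Section 2.8.2, on the per-protocol analysis, adds no separate definition: "The same procedures as those indicated for intention-to-treat analysis will be conducted".

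The first hypothesis, in section 1, is a contrast between programmes: "adapted taekwondo produces significantly greater effects on cognitive status, brain activity, health-related quality of life, and postural balance than a multi-component training and walking exercise".

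**The concern.** The numerator holds one post mean and one pre mean. That describes how far one group moved, and nothing in it refers to a second group. A within-group change also contains whatever the arms share over 16 weeks, such as practice on repeated tests, regression to the mean and time trends. A between-group contrast removes these, and the stated equation leaves them in.

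This is a rule stated wrongly, not a detail left to a fuller document: the article gives an explicit equation and says that it serves the between-group purpose. An analysis plan that followed it would repeat the error, and one that did not would depart from the published protocol. What is at stake is the size of the difference between taekwondo and the other programmes, which a significance test does not supply.

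**Working it through.** The documents state no value of d, so there is no figure to reproduce. The check is algebraic, with an illustration.

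**Inputs**
- Equation: d = (post mean − pre mean)/combined SD (section 2.8.1).
- SD: 3.38 repetitions on the chair stand test (section 2.3). That section does not say whether this is an SD of scores or of changes. It is used here only as a common scale.
- Mean changes: assumed, because the documents give none for any arm. Taekwondo is set at +3.0 repetitions and the comparator is varied from +3.0 to −1.0.

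**Formulas.** Let a be the mean change in taekwondo, b the mean change in the comparator and s the common SD.
- Stated equation, applied to taekwondo: a/s.
- Between-group d: (a − b)/s.
- The two differ by b/s, so they agree only when b = 0.

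**Numbers** (a = 3.0, s = 3.38)

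| Comparator change b | Stated equation, a/s | Between-group d, (a − b)/s |
|---|---|---|
| +3.0 | 3.0/3.38 = 0.89 | 0/3.38 = 0 |
| +1.0 | 3.0/3.38 = 0.89 | 2.0/3.38 = 0.59 |
| 0 | 3.0/3.38 = 0.89 | 3.0/3.38 = 0.89 |
| −1.0 | 3.0/3.38 = 0.89 | 4.0/3.38 = 1.18 |

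The stated equation gives the same answer in every row because b does not enter it. It is too large when the comparator improves and too small when the comparator declines.

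**Can pooling rescue the equation?** Entering the pre and post means of two equal-sized groups taken together gives their average change, (a + b)/(2s), which is not a contrast. For b = +3.0 it gives 3.0/3.38 = 0.89 where the between-group d is 0. For b = 0 it gives 1.5/3.38 = 0.44 where the between-group d is 0.89. The two agree only if a = 3b, which happens by coincidence in the +1.0 row.

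**The case against.** The strongest reply is that the trial's comparative conclusions do not rest on this equation. Section 2.8.1 plans the group × time ANOVA, Bonferroni-adjusted post-hoc tests and Fisher's exact test on responders. A reader might infer that the arms will be compared only by setting four within-arm effect sizes side by side. The documents do not support that, because the planned tests decide whether groups differ and none of them uses the d equation. This part of the reply stands in full.

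A reader might also infer that effect sizes will be inflated by a fixed amount, for example by half (0.89 against 0.59). That figure depends entirely on an assumed comparator gain of 1.0. The inflation is zero if the comparator does not change and becomes an understatement if it declines. Nor is it right that within-group values carry no comparative information. If every group is scaled by the same SD, they keep the order of the mean changes, and their difference is the between-group d: 3.0/3.38 − 1.0/3.38 = 0.888 − 0.296 = 0.592. The protocol does not say that one common SD will be used, or that this difference will be reported.

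Finally, the sentence does announce a between-group d, so the authors may intend a difference of changes or of post means, and an unseen analysis plan may define one. That is plausible, but it does not correct the printed rule, which gives one equation for both purposes.

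**Conclusion.** The point holds in a limited form. The between-group Cohen's d is wrongly defined in section 2.8.1, and section 2.8.2 carries the definition into the per-protocol analysis. The p-values from the ANOVA, the post-hoc tests and Fisher's test are not affected. The damage is confined to the reported between-group effect sizes, which are the effect sizes that bear on the first hypothesis.

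The error equals the comparator's own standardised change. In the illustration it runs from 0.89 too high (comparator +3.0) through zero to 0.30 too low (comparator −1.0; 0.89 against 1.18). These sizes rest on assumed changes and on 3.38 as a common SD. The conclusion that the equation lacks a second-group term rests on neither. The comparators in the hypothesis are active training programmes, and section 1 describes combat-sport interventions as giving outcomes similar to theirs. The one case in which the equation is correct, no change in the comparator, is therefore not one that the article gives reason to expect for those contrasts.

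**What to change.** Keep the stated equation for within-group description only. Add a separate definition: the between-group d is the difference in mean change between two groups (or the baseline-adjusted difference at week 16), divided by a named pooled SD of those two groups. State which SD is pooled. A 95% confidence interval is preferable. Report this d alongside the planned ANOVA contrasts, not in place of them, and apply the same definition in the per-protocol analysis. Settle it before the data are analysed so that the choice cannot follow the results.

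The cost is about one sentence of wording, with no new data and no change of design. Between-group effect sizes will be smaller than the stated equation would give wherever the comparator also improves.
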